### Western medication (WM) group

Betahistine mesilate tablets (6 mg per tablet; Eisai (China) Pharmaceutical Co., Ltd.; National Medical Products Administration No. H20040130) are used, one tablet each time, three tablets per day, after meals. The treatment was administered continuously for 5 days per week over a 3-week period.

### Outcome measurements

The outcome measures and evaluation time points are summarized in Table 1.

#### Primary outcome

The Dizziness Handicap Inventory (DHI) is the most widely used self-reported measure for assessing dizziness across three domains (25): physical (DHI-P, maximum score of 28), emotional (DHI-E, maximum score of 36), and functional (DHI-F, maximum score of 36). Each item is scored as 0 (no), 2 (sometimes), or 4 (yes). The total score, ranging from 0 to 100, is calculated by summing the scores of all items, with higher scores indicating more severe the dizziness disorder. These outcome measures will be repeatedly assessed at weeks 0, 3, and 11 by a researcher who is blinded to participant allocation.

#### Secondary outcomes

Secondary outcomes included the following eight items: 1) change in the Dizziness and Anxiety Rating Scale (DARS) at 0, 3, and 8 weeks; 2) changes in the total frequency of vertigo episodes over weeks 1, 3, and 8; 3) changes in the average duration of vertigo episodes over weeks 1, 3, and 8; 4) changes in the average severity of vertigo episodes over weeks 1, 3, and 8; 5) changes in the average impact on quality of life scores of vertigo episodes over weeks 1, 3, and 11.

### DARS

The DARS evaluates the degree of balance disorder and disorientation caused by dizziness. The DARS consists of 6 items, each rated on a 7-point scale: asymptomatic (0), very mild (1), mild (2), mild to moderate (3), moderate (4), moderate to severe (5), and severe (6). The total possible score ranges from 0 to 36, with higher scores indicating more severe dizziness.

### Dizziness diaries

Participants will be required to maintain a dizziness diary, recording each episode of dizziness in detail. For each episode, participants will document the attack duration, date of occurrence, vertigo intensity, impact on daily life, and any acute medications taken. Vertigo intensity will be evaluated using a VAS (0 to 10). This detailed record will facilitate the comprehensive assessment of dizziness frequency, severity, and its impact on daily activities throughout the study period.

### TCD, sMRI and ASL-MRI outcome measures

This trial will concentrate on the following TCD, sMRI and ASL-MRI indicators (week 0, and week 3). For TCD, assessment includes measuring the mean flow velocity (MFV) and resistance index (RI) in the bilateral middle cerebral arteries (MCA), anterior cerebral arteries (ACA), posterior cerebral arteries (PCA), vertebral arteries (VA), and basilar artery (BA) for TCD. For sMRI, evaluations will encompass voxel-based whole-brain voxel-mirrored homotopic connectivity (VMHC), cortical thickness, gray matter volume (GMV), white matter volume (WMV), and total brain volume (TBV). These comprehensive assessments aim to provide detailed insights into cerebrovascular function and brain structural changes over the study period. For ASL-MRI, the following image data will be acquired: high-resolution 3D T1-weighted images for delineation of gray and white matter regions of interest (including deep gray matter structures), to support ASL data analysis and spatial normalization to a standard brain atlas. The total scanning time per MRI session will be within 15 min.

### Treatment expectations assessment

Before the treatment, participants in each group will be asked, “How do you perceive the final efficacy of the treatment?” Participants will select from one of five options: 1) highly effective (symptom improvement >75%); 2) moderately effective (symptom improvement 50%–75%); 3) slightly effective (symptom improvement 25%–50%); 4) no change (symptom improvement 0–25%). Responses indicating “highly effective” will be categorized as high expectations, while all other responses will be categorized as low expectations.

To minimize expectation bias, outcome assessors and statisticians will remain fully blinded to group allocation throughout the study. In addition, treatment expectation level will be incorporated as a covariate in the statistical analysis of the primary outcome (DHI) to adjust for its potential confounding influence on subjective symptom reports. To further ensure objectivity, all assessments will be performed using standardized procedures, and expectation evaluation will be conducted by a researcher blinded to treatment assignment.

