Acupuncture, recommended by the World Health Organization (WHO) as an alternative and complementary strategy for stroke management and rehabilitation (11), has shown promising efficacy and safety for post-stroke vertigo (12). However, most studies have primarily utilized acupuncture as an adjunct to western medical treatments (e.g., betahistine, flunarizine), which makes it difficult to clearly delineate the specific therapeutic effects of acupuncture itself. The clinical effectiveness of acupuncture has been questioned due to potential psychological or placebo effects, leading to concerns about the rigor of control designs in many studies. Overall, the clinical evidence supporting acupuncture for PCIS with vertigo remains limited and generally of low quality (13). Therefore, the present study is designed to provide novel insights in two key aspects. First, by independently establishing a sham acupuncture control group and a western medication control group, this trial aims to isolate the specific therapeutic effects of acupuncture as a standalone intervention, disentangling its intrinsic efficacy from non-specific factors such as concomitant drug effects or placebo responses. Second, a treatment expectation assessment will be incorporated to quantitatively evaluate the potential influence of psychological factors on treatment outcomes, an aspect seldom addressed in previous studies.

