### Sample size calculation

As reported in previous studies (8), the mean DHI score for patients treated with betahistine mesilate was 30. For the purpose of sample size estimation, we adopted the clinically meaningful difference derived from our primary comparison: manual acupuncture versus sham acupuncture, assuming a mean DHI score of 21 in the manual acupuncture group, 33 in the sham acupuncture group, with a standard deviation of 20. A 12-point difference in DHI total score between manual acupuncture and sham acupuncture was regarded as clinically meaningful, since the minimal clinically important difference (MCID) for DHI total score has been established as 11 points (26). The trial will include three groups in a 1:1:1 ratio. Using a twotailed test with a category 1 error of 0.05 and a statistical efficacy of 90%, One-Way Analysis of Variance (ANOVA) F-Tests was employed by PASS software (Power Analysis and Sample Size, version 15). The calculations indicate that a minimum of 66 participants per group is required, totaling 198 participants across all groups. Accounting for an estimated drop out rate of 15%, the total sample size should be increased to 234 participants, with at least 78 participants per group.

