### Statistical analysis

Analyses for this study will be conducted in accordance with both the intention-to-treat (ITT) principle and the per-protocol set (PPS) approach. The ITT analysis will include all randomized participants, and the missing data will be imputed using the Last Observation Carried Forward (LOCF) method, with the most recent observed data carried forward for filling. The PPS will include participants who have completed at least 80% of the prescribed treatment. SPSS 23.0 software will be used for statistical analysis. Quantitative indicators are described using mean, standard deviation, median, 25th percentile and 75th percentile. Categorical indicators are described using frequencies and percentages.

To control the Type I error caused by multiple comparisons, the Bonferroni correction will be adopted for pairwise comparisons of the primary outcome (DHI total score) among the three groups (manual acupuncture vs. sham acupuncture, manual acupuncture vs. western medication, sham acupuncture vs. western medication), with the adjusted significance level set at *p* < 0.017 (0.05/3); for secondary outcomes (DARS scores, dizziness diary indicators including attack frequency, duration and severity), the false discovery rate (FDR) method will be used for multiple comparison correction to balance the Type I and Type II error rates in exploratory analysis of multiple secondary indicators.

Since this study is a multicenter clinical trial, sub-center and corresponding baseline values were incorporated as covariates in the generalized linear model for analysis. Additionally, binary logistic regression was employed to analyze the impact of high versus low expectations on the primary efficacy endpoint across groups. The dependent variable in this analysis was response status, defined as participants showing at least a 50% reduction in total DHI scale score from baseline after 3 weeks of treatment (referred to as responders). The independent variable was the level of expectation (high or low).

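### Treatment expectation is collected on an ordered scale but analysed as top answer versus the rest; an ordered score would adjust the DHI analysis better at almost no cost (low priority)

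*Protocol article*

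**What the plan says.** Under Treatment expectations assessment, each participant is asked before treatment how effective the treatment will be. The text announces the answer format with "Participants will select from one of five options", but lists four: above 75%, 50–75%, 25–50% and 0–25% improvement, the last labelled as no change. The values 50% and 25% each belong to two bands.

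The coding follows at once: the top answer counts as high expectation, "while all other responses will be categorized as low expectations". The next paragraph gives the variable a role in the main analysis: "treatment expectation level will be incorporated as a covariate in the statistical analysis of the primary outcome (DHI"), in order to adjust for confounding of subjective reports.

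The Statistical analysis section describes the main model differently: "sub-center and corresponding baseline values were incorporated as covariates in the generalized linear model for analysis". Expectation is not in that list. It appears in a separate logistic regression of response (at least a 50% fall in DHI total at week 3), where "The independent variable was the level of expectation (high or low").

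The Introduction presents this assessment as one of two novel features of the trial: "a treatment expectation assessment will be incorporated to quantitatively evaluate the potential influence of psychological factors on treatment outcomes".

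**The concern.** Splitting an ordered variable at its top category treats everyone below the cut as alike. Here the pooled group runs from patients expecting most of their symptoms to resolve to patients expecting nothing. If DHI depends on expectation across that range, the covariate cannot adjust for it, and the responder regression is less likely to detect an influence of expectation. A null result there could then be misread as showing that expectation played no part.

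This is a stated rule, not a detail left for a later document: the cut is fixed, no reason is given for it, and the variable is named for the primary outcome analysis. The two sections also disagree on whether expectation is in that analysis at all.

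**Working it through.** **Inputs from the protocol article.** Four listed bands, cut at the top (Treatment expectations assessment). Means of 21 (manual acupuncture), 33 (sham) and 30 (betahistine), SD 20, two-sided 0.05, 90% power, 15% dropout (Sample size calculation). Bonferroni level 0.05/3 for pairwise DHI comparisons (Statistical analysis).

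**Assumed, because the document gives no figure.** The share choosing each answer, equal spacing of the levels (scores 3, 2, 1, 0), and the correlation ρ between expectation and DHI.

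**The plan's own figure.** The means average 28, and the squared deviations sum to 49 + 25 + 4 = 78. At n = 66 the noncentrality is 66 × 78 / 400 = 12.87, and the one-way ANOVA power is 0.9005 (0.8957 at n = 65). Then 198 / 0.85 = 232.9, or 78 per group and 234 in all. The stated sample size reproduces. It uses no covariate, so nothing below changes it. The document gives no figure for the effect of the split.

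**Variance of the score kept by the split.** With q the share giving the top answer and m the mean score of the rest,

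kept = q(1 − q)(3 − m)² / Var(score).

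Worked case, equal use of the four answers: q = 0.25, m = 1, so 0.1875 × 4 = 0.75; Var = 1.25; kept = 0.60.

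| Assumed shares, top to bottom | Kept | Lost |
|---|---|---|
| 10 / 40 / 35 / 15% | 0.36 | 64% |
| 20 / 50 / 20 / 10% | 0.47 | 53% |
| 25 / 25 / 25 / 25% | 0.60 | 40% |
| 30 / 35 / 25 / 10% | 0.61 | 39% |
| 50 / 30 / 15 / 5% | 0.71 | 29% |
| 60 / 30 / 8 / 2% | 0.77 | 23% |

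Outside that range, 5 / 35 / 40 / 20% loses 77% and 80 / 15 / 4 / 1% loses 19%. The limits are 0% (only the top answer and one other are used) and 100% (nobody gives the top answer). Against a latent normal expectation the loss is 66% when 10% are above the cut and 36% when 50% are.

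**Effect on manual versus sham acupuncture.** The residual SD is 20√(1 − ρ²k), with k = 1 for the ordered score and k = 1/3 for the split (slightly worse than the worst row above). The difference is 12, n = 66 per arm, level 0.05/3.

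| ρ | Ordered score | High/low |
|---|---|---|
| 0.1 | 85.8% | 85.5% |
| 0.2 | 86.9% | 85.9% |
| 0.3 | 88.9% | 86.6% |

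At ρ = 0.3 the residual SDs are 20√0.91 = 19.08 and 20√0.97 = 19.70. The gap in power is 0.3, 1.0 and 2.3 points.

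**Effect on adjustment, as an illustration only.** Assume 5 DHI points per expectation level.
- Shares of 30/40/20/10% in one arm and 20/30/30/20% in the other give mean scores of 1.9 and 1.5, hence 5 × 0.4 = 2.0 points of imbalance. Adjusting for high/low leaves 1.15 of them (57%).
- Shares of 30/40/20/10% and 30/20/30/20% differ only below the cut. The imbalance is 5 × (1.9 − 1.6) = 1.5 points, and high/low removes none of it.

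Under this linear assumption the ordered score removes all of the imbalance in both cases.

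**The case against.** Four objections carry weight.

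- **The percentages are not facts about the trial.** A reader might infer that the plan throws away a quarter to two thirds of its information. The document does not support this. The figures depend on assumed response shares and equal spacing, and they concern the variance of a covariate, not information on the treatment effect. The split is also a recoding, so the original answers can still be used.
- **The primary comparison is hardly touched.** Manual versus sham acupuncture is randomised with participants blinded in both arms, so coarse coding there costs mainly a little precision. This stands and sets the priority.
- **Harm to the comparison with the unblinded medication arm is unproven.** A reader might take this to be where the split does most damage. The question is asked before treatment, and Table 1 puts it in the same column as randomisation, which does not settle whether the participant already knows the allocation. If not, randomisation balances expectation on average. If so, expectation is a post-randomisation variable, and finer adjustment may remove part of the contrast instead of a bias. That comparison is also secondary.
- **The binary form of the DHI covariate is inferred.** The text speaks of expectation level, and high or low is spelled out as a model term only for the responder regression. The inference is strong, because high and low are the only levels defined, but it remains an inference.

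The protocol also does not claim complete control: its Discussion says that assessing expectation cannot fully exclude expectancy effects. What survives is narrower: a fixed rule uses less of the answer than it could, with no stated reason, and two sections disagree on where the variable is used.

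**Conclusion.** The point holds as a low-priority improvement. The top-category split is stated, and so is the covariate role in the primary DHI analysis; the main model's covariate list contradicts the latter. With 10% to 60% giving the top answer and equally spaced levels, both assumed, the split keeps about 36% to 77% of the variance of the four-level score. For ρ up to 0.3, also assumed, this costs about 2 power points or less in manual versus sham acupuncture and leaves the sample size unchanged. The practical loss is less complete adjustment where arms differ in expectation, and a less sensitive expectation analysis. Nothing here invalidates the primary comparison.

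**What to change.** Three edits, using the same question and the same data:

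1. Settle the option list: four or five answers, with bands that do not share limits at 25% and 50%.
2. Reconcile Treatment expectations assessment with Statistical analysis, so that expectation is listed once as a covariate in the DHI model, beside centre and baseline.
3. Enter expectation as an ordered score in the DHI model and in the responder regression. Keep high/low for description or as a sensitivity analysis.

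The score takes one degree of freedom, the same as the high/low indicator. Its price is the assumption of roughly equal spacing. A factor with all levels avoids that but could be sparse: with 2% to 5% in the lowest category, as in two of the distributions above, an arm of 66 would hold about 1 to 3 such patients (0.02 × 66 = 1.3; 0.05 × 66 = 3.3), which is awkward in the logistic regression. The ordered score is therefore the better default.

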**Figure 1 fig1:**
[figure not shown]
Research flow chart.

**Table 1 tab1:** Study schedule for data measurements.

Study period	Baseline	Allocation	Intervention period	Follow-up period
Time point (week)	−1	0	3	11
Enrolment and Baseline data:	Eligibility screen; informed consent; demographic characteristics; disease/combination medication history	Randomization		
Primary outcome:		DHI	DHI	DHI
Secondary outcomes:		DARS; dizziness diaries	DARS; dizziness diaries; adherence assessment	DARS; dizziness diaries
Objective hemodynamic/ imaging indicators:		TCDsMRIASL-MRI	TCDsMRIASL-MRI	
Other assessments:		Treatment expectations assessment	Safety assessment	Safety assessment

DHI, Dizziness Handicap Inventory; DARS, Dizziness and Anxiety Rating Scale; TCD, transcranial Doppler; sMRI, structural magnetic resonance imaging; ASL-MRI, arterial spin labeling MRI.

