### Randomization and blinding

A random number will be generated with the R software (V.4.3.3) and concealed in opaque random envelopes. The envelopes will be prepared by a third party in advance, with the sequence number labeled on the surface and the random number and group allocation information sealed in. The random envelopes will be preserved by special personnel who are not involved in treatment and evaluation. Participants are randomly assigned in a ratio of 1:1:1 to manual acupuncture (MA) group, sham acupuncture (SA) group, and western medication (WM) group.

Given the use of two distinct acupuncture techniques in this trial, the acupuncturist will be aware of the group allocation for each participant. However, identical auxiliary devices will be used in both the acupuncture and sham acupuncture groups to maintain blinding for participants. Participants in both groups will remain unaware of their specific group assignment. Furthermore, outcome assessors and statisticians will be blinded to group allocations throughout the study to minimize bias. To maintain blinding, all researchers will undergo identical training prior to the trial, and treatments will be administered in separate rooms for each participant. It should be noted that participants in the medication group will not be blinded.

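### Expectation may be recorded after allocation while medication participants are unblinded, so adjusting DHI for it can distort the medication comparisons; the responder model names no arm term

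*Protocol article*

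**What the plan says.** **Treatment expectations assessment.** "Before the treatment, participants in each group will be asked" how effective they think the treatment will finally be, and the answers are reduced to high or low. The section adds that "expectation evaluation will be conducted by a researcher blinded to treatment assignment". It then states that "treatment expectation level will be incorporated as a covariate in the statistical analysis of the primary outcome (DHI"), on the ground that expectation may confound subjective symptom reports.

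**Table 1.** The entry "Treatment expectations assessment" stands in the week-0 column headed allocation, which also holds randomization. Baseline DHI, DARS, diaries, TCD and MRI are in the same column. Consent, screening and history are in the week −1 column.

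**Randomization and blinding.** Of the manual and sham arms: "Participants in both groups will remain unaware of their specific group assignment". By contrast, "participants in the medication group will not be blinded".

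**Statistical analysis.** For the main model, "sub-center and corresponding baseline values were incorporated as covariates in the generalized linear model for analysis". Expectation is not in that list. A logistic regression then takes as outcome a DHI total at least halved after 3 weeks: "The independent variable was the level of expectation (high or low"). No arm, centre or baseline term is named for it.

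**The concern.** A covariate is safe to adjust for in a randomized comparison when allocation cannot have influenced it. If expectation is recorded once participants know they will take tablets, their answer is partly a response to the allocation. Adjusting for it then removes or distorts part of the manual versus medication and sham versus medication contrasts. Blinding the interviewer does not help, because it is the respondent who knows.

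Manual versus medication is the stated secondary objective, and two of the three Bonferroni-tested DHI comparisons involve the medication arm.

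The responder model raises a separate problem. With expectation as its only predictor and all arms pooled, any difference in response between arms that differ in expectation is credited to expectation. The Introduction presents the expectation assessment as one of the trial's two novel features, so this result is likely to be reported.

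**Working it through.** **1. The plan's own figure.** The planning means are 21 (manual), 33 (sham) and 30 (betahistine), with SD 20. The grand mean is 28 and the squared deviations sum to 49 + 25 + 4 = 78. The noncentrality at 66 per group is 66 × 78/400 = 12.87, and the one-way F-test at 0.05 has power 0.9005. With 15% dropout, 66/0.85 = 77.6, so 78 per group and 234 in all. The sample size reproduces. The present point does not depend on it, but the means give a scale: manual versus medication 30 − 21 = 9, manual versus sham 33 − 21 = 12.

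**2. When is expectation recorded?** Three things suggest that allocation has already happened: the question goes to participants in each group, it concerns the treatment in the singular, and Table 1 places it beside randomization. Against that, baseline DHI stands in the same column. The column therefore does not fix the order within week 0.

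**3. Effect of the DHI adjustment.** The documents give no expectation data, so these inputs are assumed. Let high expectation go with g fewer DHI points, and let the share with high expectation differ by d between manual and medication because the latter know their arm. The adjusted contrast shifts by g × d:

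- g = 6, d = 0.60 − 0.30: 1.8 points, which is 1.8/9 = 20% of the planned difference and 1.8/20 = 0.09 SD.
- g = 5 to 15, d = 0 to 0.4: 0 to 6 points.

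A simulation with 66 per arm, 2000 runs, g = 10 and 50% high expectation in both acupuncture arms gave these mean differences:

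| High expectation, medication | Medication − manual, unadjusted → adjusted | Sham − manual, unadjusted → adjusted |
|---|---|---|
| 50% | 8.93 → 8.94 | 12.04 → 12.01 |
| 30% | 9.11 → 7.12 | 12.11 → 12.11 |
| 20% | 9.00 → 5.99 | 12.06 → 12.06 |

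Sham versus medication moves too. In the second row it goes from 12.11 − 9.11 = 3.00 to 12.11 − 7.12 = 4.99. If medication participants expected more rather than less, the shifts would change sign.

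**4. Responder model without arm.** Suppose expectation has no effect inside any arm. With equal arms, response among high-expectation participants is Σ(p·r)/Σp and among low-expectation participants Σ((1−p)·r)/Σ(1−p), where p is the share with high expectation and r the response rate. Rates below are assumed, in the order manual/sham/medication:

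| Response r (%) | High expectation p (%) | High vs low response | Odds ratio |
|---|---|---|---|
| 50/30/30 | 50/50/50 | 0.367 vs 0.367 | 1.00 |
| 65/30/45 | 70/70/20 | 0.755/1.6 = 0.472 vs 0.645/1.4 = 0.461 | 1.05 |
| 50/30/30 | 50/50/30 | 0.49/1.3 = 0.377 vs 0.61/1.7 = 0.359 | 1.08 |
| 50/30/30 | 50/50/20 | 0.46/1.2 = 0.383 vs 0.64/1.8 = 0.356 | 1.13 |
| 65/45/30 | 60/60/30 | 0.75/1.5 = 0.500 vs 0.65/1.5 = 0.433 | 1.31 |
| 65/45/30 | 70/70/20 | 0.83/1.6 = 0.519 vs 0.57/1.4 = 0.407 | 1.57 |

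The correct answer is 1.00 in every row. If the third row had 70% high expectation in the medication arm instead of 30%, the high and low groups would swap and the odds ratio would be 1/1.08 = 0.93.

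**The case against.** **Timing.** A reader might infer that expectation is certainly asked after allocation. The article does not say so. It says only that the question precedes treatment, and the same reading of Table 1 would make baseline DHI a post-allocation measure. This stands: the supportable statement is that the order is open and the wording points towards after allocation.

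**The primary comparison.** A reader might infer that the main efficacy result is biased. It is not, on this ground. Manual and sham participants do not know which they will receive and answer before the first session, so expectation should not depend on that allocation. There it acts as an ordinary prognostic covariate. This stands in full.

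**Two conflicting primary models.** The two sections can be read as additive: centre, baseline and expectation. Statistical analysis does not call its list complete. So this is a mismatch to be aligned, not proof of two rival models. It still leaves open whether expectation is in the DHI model.

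**The responder model.** It is ancillary, and its reference to the impact across groups could mean a separate fit in each arm, which would remove the mixing. That is possible, but no stratification is stated.

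**Size.** The odds ratio of 1.57 rests on a response rate for medication well below sham (30% versus 45%), whereas the planning means put betahistine slightly better than sham (30 versus 33, lower being better). It is the top of an assumed range, not an expected value.

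**Disclosure.** The limitations already name expectation bias from the unblinded arm. They do not connect it to the adjustment.

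**Deliberate adjustment.** It could be argued that removing the part of the effect that runs through expectation is the purpose. That is a different question from the randomized contrast. It needs the further assumption that nothing unmeasured drives both expectation and DHI, and the article describes the term as an adjustment for confounding.

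**Conclusion.** The point holds for the comparisons with medication and for the responder model, not for manual versus sham. If expectation is recorded after allocation, adjusting DHI for it can move the medication contrasts by 0 to 6 points under the assumed inputs, against a planned manual versus medication difference of 9. The shift is zero if expectation is balanced across arms, and its direction is unknown.

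If the responder model is pooled over arms as its wording allows, it can return an odds ratio of about 1.0 to 1.6 with no expectation effect inside any arm. It returns 1.0 when expectation is balanced and can fall below 1 if medication participants expect more. The covariate list under Statistical analysis lacks the expectation term that the expectations section requires.

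The mechanism follows from the text; the sizes rest on assumed rates. The primary conclusion is not shown to be at risk. The correction is cheap and protects a stated secondary objective.

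**What to change.** 1. State that the expectation question is asked after consent and before the envelope is opened, and word it for the trial treatments, in general or one by one. This moves one question within the same visit. The small downside is that it no longer measures expectation of the assigned treatment.
2. If that is not possible, for instance because recruitment is under way, leave expectation out of the DHI model for both comparisons with medication and use it there only as a sensitivity analysis. It can stay as a covariate for manual versus sham.
3. Give the same covariate list in the expectations section and under Statistical analysis.
4. Add arm, centre and baseline DHI to the responder model, with an arm × expectation term as an exploratory addition. This costs a few model terms and no new data.
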